### Randomization

The randomization procedure will be website-based using random blocks and stratified by the response to a suprathreshold levodopa dose administered in off-drug phase. This response is measured as the ratio of the MDS-UPDRS part III score in on-/off-drug phases. The response to levodopa is a good indicator of the effect of DBS. A cutoff of 40% improvement in MDS-UPDRS in on-drug phase was used to separate the two stratification groups. The cutoff is based on the median improvement of patients treated with DBS in the STN in a previous nationwide study on the effectiveness of DBS in patients with PD [24]. The web-based method of randomization will provide concealment allocation and prevent the risk of selection bias. Participants will be randomized using TENALEA, which is an online, centralized randomization service. Allocation concealment will be ensured because the service will not release the randomization code until the patient has been recruited into the trial, which takes place after all baseline measurements have been completed, as shown in Additional file 1: Figure S1.

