#### Secondary outcome measures

Secondary endpoints are the efficacy of treatment on the following:Motor symptoms as measured by MDS-UPDRS part III and the Clinical Dyskinesia Rating Scale [29]Daily functioning measured with MDS-UPDRS part IINonmotor experiences of daily living as measured by MDS-UPDRS part IFunctional health status measured with the Academic Medical Center Linear Disability Score [30]Quality of life measured with the 39-item Parkinson’s Disease Questionnaire (PDQ-39) [31]Treatment satisfactionBurden of therapySurgical timeDuration of hospital admittanceSurgery- and stimulation-related side effectsPD medication changesOther motor complications measured with UPDRS part IVOther psychiatric adverse effects as measured with the Hamilton Depression Rating Scale [32], Hamilton Anxiety Rating Scale [33], Columbia Suicide Severity Rating Scale [34], Starkstein Apathy Scale [35], and Young Mania Rating Scale [36]

*See* Additional file 3: Table S2 for further details.

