### Sample size calculation

We estimate that by performing DBS surgery under general anesthesia, a relative reduction of 50% in cognitive, mood, and behavioral adverse effects will be achieved. To detect a relative reduction of 50% (52% local anesthesia versus 26% general anesthesia) using a chi-square test with an α value of 0.05 (two-sided) and β value of 0.2, we estimated that 110 patients (55 in each treatment group) would be needed. We expect adequate participant enrollment to reach our target sample size because we operate on 80 patients with PD per year. Furthermore, in our previous clinical trials, we have always been able to reach an inclusion ratio of 70% when studying patients with PD.

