### Statistical analysis

Statistical analyses will be based on the intention-to-treat principle. Baseline assessments and outcome parameters will be summarized using simple descriptive statistics. Change scores are calculated as the score at follow-up minus the score at baseline. To test the hypothesis that STN DBS under general anesthesia produces fewer patients with significant postoperative cognitive, mood, and behavioral adverse effects, the primary outcome score will be compared using a chi-square test. Adjustments for factors that differ at randomization, including the stratification variable, will be made using regression or multilevel models. Effect sizes will be expressed as ORs. We will perform additional per-protocol and as-treated analyses.

The mean change in MDS-UPDRS Part III scores from baseline to follow-up at 6 months will be analyzed using a two-group *t* test. With regard to the comparisons of the other secondary outcomes, we will use the appropriate parametric and nonparametric statistics. Additionally, we will focus on the MDS-UPDRS part III scores at 6 months using multivariable linear regression, including the stratification variable and other factors that differ at randomization, in the model. In all analyses, statistical uncertainty will be expressed with 95% CIs. *P* values < 0.05 will be considered statistically significant. We will perform additional per-protocol and as-treated analyses. A fully specified statistical analysis plan will be written and approved before unlocking the data blinding, provided in the form of a *Trials* Update article.

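### MDS-UPDRS III: baseline score enters the 6-month regression only if it happens to differ between arms; always including it would gain precision at no data cost

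*Protocol article*

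**What the plan says.** All of this is in the protocol article.

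- **Status of the endpoint.** Secondary outcome measures lists "Motor symptoms as measured by MDS-UPDRS part III and the Clinical Dyskinesia Rating Scale" among the secondary endpoints.
- **First analysis.** Statistical analysis: "The mean change in MDS-UPDRS Part III scores from baseline to follow-up at 6 months will be analyzed using a two-group" t test. The same section defines change by simple subtraction: "Change scores are calculated as the score at follow-up minus the score at baseline".
- **Second analysis.** "Additionally, we will focus on the MDS-UPDRS part III scores at 6 months using multivariable linear regression". The covariates of that model are described as follows: "including the stratification variable and other factors that differ at randomization, in the model". The stratification variable is therefore always in this model. Anything else, including baseline MDS-UPDRS III, is in it only if it differs between the arms. What counts as differing is not defined.
- **Stratification variable.** Randomization: "This response is measured as the ratio of the MDS-UPDRS part III score in on-/off-drug phases". On how patients were then grouped, the section adds: "A cutoff of 40% improvement in MDS-UPDRS in on-drug phase was used to separate the two stratification groups". It is a two-level measure of levodopa response, not of baseline severity.
- **Later plan.** The Statistical analysis section announces a complete analysis plan, to be approved before unblinding.

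**The concern.** In a randomized trial, the gain from adjusting for a covariate comes from how strongly it predicts the outcome, not from whether the arms differ on it. The baseline value of a rating scale is usually among the best predictors of the later value. The article uses it in two limited ways: subtracted with a fixed coefficient of 1 in the t test, or entered in the regression only when imbalance triggers it. The stratum cannot replace it, because two patients with the same on/off ratio can have very different scores.

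The two analyses can also disagree. If the baseline means differ by d points and d is too small to count as differing, the estimate from change equals the estimate from the 6-month score minus d (ignoring the stratum term). One standard error of d with 55 per arm is √(2/55) = 0.19 baseline SD, which would pass unremarked. A model that always includes baseline avoids having to choose between the two.

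The Abstract and Background make motor and functional benefit on a par with awake surgery one of the aims. A judgement of comparability depends on the width of the confidence interval, and the sample size was set for the binary primary outcome only.

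**Working it through.** **1. The plan's own figure.** The article gives no calculation for MDS-UPDRS III. Its only one is for the primary outcome: 52% versus 26%, "using a chi-square test with an α value of 0.05 (two-sided) and β value of 0.2". With pooled variance and no continuity correction, mean proportion 0.39:

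n per arm = [1.96·√(2·0.39·0.61) + 0.8416·√(0.52·0.48 + 0.26·0.74)]² / 0.26² = (1.352 + 0.560)² / 0.0676 ≈ 54.1, rounded up to 55, so 110 in total (power 80.7%).

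The stated figure reproduces, and nothing below changes it.

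**2. Variance of each analysis.** Let s0 and s1 be the baseline and follow-up SDs and ρ their correlation. Per-patient variances are:

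- change score: s0² + s1² − 2ρ·s0·s1
- 6-month score without baseline: s1²
- 6-month score with baseline (ANCOVA, large sample): s1²(1 − ρ²)

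Change minus ANCOVA is (s0 − ρ·s1)², which is never negative and is zero only at ρ = s0/s1. The 6-month score minus ANCOVA is ρ²·s1², also never negative. So the direction does not depend on the inputs, but the size does.

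**3. Equal SDs (assumption), ρ from 0.3 to 0.7 (assumption).** ANCOVA/change reduces to (1 + ρ)/2. Half-widths are 1.96·√(2·variance/55), in SD units.

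| ρ | Change | ANCOVA | Ratio | 95% half-width, change | 95% half-width, ANCOVA | Variance saved against 6-month score alone |
|---|---|---|---|---|---|---|
| 0.3 | 1.40 | 0.91 | 0.65 | 0.44 | 0.36 | 9% |
| 0.5 | 1.00 | 0.75 | 0.75 | 0.37 | 0.32 | 25% |
| 0.7 | 0.60 | 0.51 | 0.85 | 0.29 | 0.27 | 49% |

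Expressed as patients, 1/0.85 = 1.18 and 1/0.65 = 1.54: the t test would need 18% to 54% more for equal precision.

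**4. Unequal SDs.** ANCOVA/change ratios:

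| s1/s0 | ρ = 0.3 | ρ = 0.5 | ρ = 0.7 |
|---|---|---|---|
| 0.8 | 0.50 | 0.57 | 0.63 |
| 1.2 | 0.76 | 0.87 | 0.97 |

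For example, with s1 = 1, s1/s0 = 1.2 and ρ = 0.7: change = 1 + 0.694 − 1.167 = 0.528, ANCOVA = 0.51, ratio 0.97. At this SD ratio the gain disappears at ρ = 1/1.2 = 0.83.

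**5. The rule of adjusting only if baseline differs.** Simulation: 8,000 trials per setting, 55 per arm, equal SDs, no stratum term, and differing taken as p < 0.05. That threshold is an assumption. Baseline entered in about 5% of trials. Power for an illustrative difference of 0.5 SD:

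| ρ | Rule | Baseline always included |
|---|---|---|
| 0.3 | 74% | 77% |
| 0.5 | 74% | 85% |
| 0.7 | 77% | 95% |

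With no true difference, the rule rejected in 4.8%, 4.5% and 3.5% of trials. It does not inflate the type I error and is conservative at ρ = 0.7.

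**The case against.** The strongest reply is that nothing here is an error. The t test on change uses baseline and is unbiased under randomization, the endpoint is secondary, and the article does not rank one motor analysis above the other. The regression also deals with the case where baseline is visibly imbalanced, and a full analysis plan is to follow. All of this stands except the last step. The article does not leave the covariates open. It fixes a test and a covariate rule, and a plan that follows it would inherit both. Adjusting on visible imbalance also recovers no precision when the arms look balanced.

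Some stronger readings are tempting but not supported:

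- **That the t test is biased or invalid.** It is neither.
- **That change scores always have larger variance when the correlation is below 1, by the factor (1 + ρ)/2.** That factor needs equal SDs. With a larger follow-up SD the loss can be near zero.
- **That the loss can be stated in MDS-UPDRS points.** The article gives no SD for the scale, and no motor margin against which to judge a wider interval.
- **That every continuous scale is affected.** For the other secondary outcomes the article leaves the choice of method open, so there is no fixed rule to criticise.

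**Conclusion.** The point holds as one of efficiency and prespecification on a secondary endpoint. Under the stated rules, baseline MDS-UPDRS III is either subtracted or admitted to the model on the strength of observed imbalance. In large samples, neither is more precise than a model that always contains it. The variance ratio is 0.65 to 0.85 with equal SDs and ρ of 0.3 to 0.7, and about 0.50 to 0.97 if the follow-up SD is 0.8 to 1.2 times the baseline SD. The correlation, the SD ratio and the simulation's trigger of p < 0.05 are assumptions, and the article supplies none of them. The stratum may carry some baseline information, which would reduce the gain over the regression slightly. A reader might infer that the trial's main conclusion or its size is at risk. They are not: the primary chi-square comparison and N = 110 are untouched. Nor do the documents show that any conclusion on motor comparability would change.

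**What to change.** Prespecify, in the analysis plan still to be written, that MDS-UPDRS III at 6 months is analysed by linear regression (ANCOVA) on three terms:

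- treatment arm
- baseline MDS-UPDRS III, measured in the same drug state as the outcome
- the levodopa-response stratification factor

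All three are included regardless of observed imbalance, and the condition that other factors must differ is dropped for this model. Report the adjusted difference with its 95% CI as the main motor result, and keep the change-score t test as supportive only. Naming the drug state matters because the Randomization section shows that the scale is scored both on and off drug.

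The cost is wording. The Randomization section says baseline measurements are complete before allocation is released, so no new data are needed, and the change can be made before unblinding.

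### The additional motor regression, on its natural reading, adjusts for levodopa response only as a two-level stratum; adding the measured continuous response would bring a small, nearly free gain in precision

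*Protocol article*

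**What the plan says.** The Randomization section of the protocol article says allocation is "stratified by the response to a suprathreshold levodopa dose administered in off-drug phase". On the scale it says: "This response is measured as the ratio of the MDS-UPDRS part III score in on-/off-drug phases". On the role of the variable: "The response to levodopa is a good indicator of the effect of DBS". On the strata: "A cutoff of 40% improvement in MDS-UPDRS in on-drug phase was used to separate the two stratification groups". On the choice of cut: "The cutoff is based on the median improvement of patients treated with DBS in the STN in a previous nationwide study".

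The Statistical analysis section gives two motor analyses. The mean change in MDS-UPDRS part III to 6 months "will be analyzed using a two-group *t* test". In addition, the 6-month score is examined with "multivariable linear regression, including the stratification variable and other factors that differ at randomization, in the model". The section closes by deferring detail: "A fully specified statistical analysis plan will be written and approved before unlocking the data blinding".

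**The concern.** Stratified randomization needs categories; a linear model does not. If the regression takes over the randomization factor as it stands, patients with 41% and 80% improvement on levodopa are treated as alike, while patients with 39% and 41% are treated as different. The one baseline variable that the article singles out as informative would then enter in a coarsened form, although the finer value is already on file for every randomized patient.

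Precision on this endpoint matters because one stated aim is that surgery under general anesthesia gives symptomatic improvement comparable to awake surgery, and the general anesthesia arm goes without macroelectrode test stimulation. A statement of comparability depends on how narrow the confidence interval is, and the 110 patients were sized for the composite primary outcome, not for the motor score.

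**Working it through.** **The plan's own figure.** The only design figure in the article is the sample size. With 52% versus 26%, two-sided α 0.05, power 80%, pooled variance and no continuity correction:

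n per arm = [1.960·√(2·0.39·0.61) + 0.842·√(0.52·0.48 + 0.26·0.74)]² / 0.26² = 54.05, rounded up to 55, so 110 in total (power 80.7% at 55 per arm).

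The figure reproduces, and the present point does not touch it. The article gives no figure for the prognostic strength of levodopa response or for the power of the motor regression.

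**Inputs for the check.** From the article: 55 per arm, two groups cut at 40%, and a cut taken from a median in an earlier study. Assumed, because the article does not give them: the split in this trial, the distribution of the response, a linear relation with the outcome, and ρ, the correlation between levodopa response and the 6-month score. If other covariates are in the model, ρ is the partial correlation given them.

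**Step 1: share of the covariate's R² kept after a cut.** For a normal covariate with proportion p below the cut, the share kept is φ(z_p)² / [p(1 − p)].

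- p = 0.5: 0.3989² / 0.25 = 0.637 (= 2/π), so 36.3% is lost
- 40:60 split: 37.8% lost
- 30:70 split: 42.4% lost
- 20:80 split: 51.0% lost

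For other shapes at a median split, the loss is 25% (uniform), about 33% (beta(4,4)) and about 46% (t with 5 degrees of freedom). The range is therefore about 25% to 51%.

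**Step 2: effect on the treatment comparison.** With outcome variance set to 1, residual variance is 1 − ρ² with the continuous response and 1 − 0.637ρ² with the two-level stratum. The standard error ratio is the square root of the variance ratio. The equivalent number of patients is 110 × (variance ratio − 1). The power column takes an effect for which the continuous model has 80% power and computes Φ(2.802/SE ratio − 1.960).

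| Assumed ρ | Continuous | Two-level | Variance ratio | SE increase | Equivalent patients | Power, two-level |
|---|---|---|---|---|---|---|
| 0.2 | 0.960 | 0.975 | 1.015 | 0.8% | 1.7 | 79.4% |
| 0.3 | 0.910 | 0.943 | 1.036 | 1.8% | 4.0 | 78.6% |
| 0.4 | 0.840 | 0.898 | 1.069 | 3.4% | 7.6 | 77.3% |
| 0.5 | 0.750 | 0.841 | 1.121 | 5.9% | 13.3 | 75.4% |
| 0.6 | 0.640 | 0.771 | 1.204 | 9.7% | 22.5 | 72.3% |

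Example at ρ = 0.5: 2.802/1.059 = 2.646, and Φ(2.646 − 1.960) = 0.754.

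**Step 3: what the stratum already achieves.** At ρ = 0.5 and for the same effect, an analysis of the 6-month score without any adjustment would have 67.9% power, against 75.4% with the stratum and 80% with the continuous response. The stratum thus recovers 7.5 of the 12.1 points available.

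**The case against.** The strongest case against is that nothing here is wrong. Adjusting for the factor used in randomization is standard, and it introduces neither bias nor a type I error problem. The coding of a covariate is a detail that a protocol may leave to the SAP, and this article defers full specification to one. The article also never says that the response enters only as two groups: it describes the stratifier first as a response measured as a ratio and only then forms groups, and the ratio could come in as a covariate found imbalanced at baseline. Finally, the regression is an additional analysis of a secondary outcome, and the motor analysis named first is an unadjusted t test.

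Most of this stands, and it limits the point to a matter of efficiency with an inferred coding. It does not remove it. The term used in the analysis section ordinarily means the two-level randomization factor, and an SAP that follows that wording literally inherits the cut. Entry through baseline imbalance depends on chance, and stratifying on the variable makes such imbalance less likely.

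A reader might infer more. One inference is that a third of the trial's precision is thrown away. The third is a share of this covariate's own R², and the standard error moves far less. Another is that the interval for the main motor comparison is widened. The t test uses no covariate, so it is unchanged by either coding. The article supports neither inference, and it gives no correlation from which a firm loss could be stated.

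**Conclusion.** The point holds as a modest inefficiency in the additional MDS-UPDRS part III regression, not as an error. The best single estimate of the loss, 36% of the covariate's own explained variance, rests on a near-median split, approximate normality and linearity. The near-median split is itself uncertain. The cut comes from an earlier study's median, the article does not say whether that improvement was with levodopa or with stimulation, and the present patients may differ.

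For a (partial) correlation of 0.2 to 0.5, the cost is a standard error about 1% to 6% larger, or 0.6 to 4.6 points of power from 80%. The upper end needs a strong correlation. If the baseline motor score is also in the model, the partial correlation could be smaller, which points towards the lower end. Validity of the regression, the primary chi-square test and the sample size are not in question. The priority is optional: worth taking because the value is already collected, but not a condition for the analysis to be sound.

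**What to change.** In the Statistical analysis section and in the forthcoming SAP, before unblinding, state that the linear regression of the 6-month MDS-UPDRS part III score includes levodopa response as continuous percent improvement in addition to the 40% stratum indicator. Keeping the indicator respects the stratified design. The sentence also removes the doubt about coding, so that two analysts would fit the same model.

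The cost is one sentence, no new data and one degree of freedom. With intercept, treatment and stratum, the residual degrees of freedom fall from 110 − 3 = 107 to 110 − 4 = 106. At the lowest assumed correlations the gain is also small, which is a further reason to treat this as optional.

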### Data safety analysis

An interim analysis will be performed by a data and safety monitoring board (DSMB) when half of the patients (*n* = 55) are enrolled. In this analysis, unblinded data are assessed, and the DSMB can advise on adjusting the study conduct, design, or sample size or on whether to terminate the study. The justifications for a recommendation to terminate the study due to clear harm will be based on data showing a notable increase of (serious) adverse events (including cognitive, mood, and behavioral adverse effects) in the general anesthesia group.

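### The interim clause lets unblinded data steer sample size or design while the final test stays at an unadjusted 0.05, and the look would come too early to guide re-sizing

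*Protocol article*

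**What the plan says.** Under Data safety analysis, the protocol article states: "An interim analysis will be performed by a data and safety monitoring board (DSMB) when half of the patients" have been enrolled, that is, 55 of 110. It continues: "In this analysis, unblinded data are assessed, and the DSMB can advise on adjusting the study conduct, design, or sample size". The board may also advise ending the trial. The only ground described for that is clear harm, shown by a marked excess of (serious) adverse events in the general anesthesia arm. Cognitive, mood and behavioral effects are expressly counted among those events. No ground or rule is given for changing the design or the sample size.

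Under Sample size calculation, the 110 patients are derived "using a chi-square test with an α value of 0.05 (two-sided) and β value of 0.2", for rates of "52% local anesthesia versus 26% general anesthesia". Under Statistical analysis, the primary outcome is compared by a chi-square test and P "values < 0.05 will be considered statistically significant". The same section promises: "A fully specified statistical analysis plan will be written and approved before unlocking the data blinding".

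The Abstract puts the measurement of the primary composite at 6 months after surgery.

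**The concern.** Two separate matters are at stake.

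**Error control.** A fixed-sample chi-square test at 0.05 holds its level when the sample size does not depend on the observed treatment difference. Here a board that has seen the arms compared on components of the primary endpoint may advise a new sample size, with no stated limit or method, and the final threshold does not change. That can weaken the trial's one confirmatory test, and it cannot be undone once a change has been made on that basis.

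**Precision.** The look is set by enrolment, but the full composite takes 6 months. The number of patients with a complete primary outcome at that moment is well below 55. If those data guided the sample size, the decision would rest on a very noisy estimate.

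**Working it through.** **1. The plan's own figure.** Rates 0.52 and 0.26, mean 0.39, difference 0.26, two-sided 0.05, power 80%:

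n per arm = [1.96 × √(2 × 0.39 × 0.61) + 0.8416 × √(0.52 × 0.48 + 0.26 × 0.74)]² / 0.26² = [1.352 + 0.560]² / 0.0676 ≈ 54.05, rounded up to 55.

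The stated 110 reproduces exactly. It uses the whole 0.05, so nothing is held back for an adaptation.

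**2. Patients with a complete 6-month composite at the look.** Evaluable = 55 − monthly accrual × 6.

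| Source of accrual rate | Per month | Evaluable | Share of 110 |
|---|---|---|---|
| 110 over 2.5 years (Abstract) | 110/30 = 3.67 | 55 − 22 = 33 | 30% |
| 80 operations a year × 70% inclusion = 56 a year (Sample size calculation) | 56/12 = 4.67 | 55 − 28 = 27 | 25% |

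This assumes steady accrual and surgery at randomization. With an assumed wait of 1-2 months for surgery, and allowing also for accrual in 24 months, the range becomes about 18-29.

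**3. Precision at that point.** With 27 patients (13.5 per arm) and 33 patients (16.5 per arm), the 95% half-width of the risk difference is:

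- unpooled variance: 1.96 × √(0.442/13.5) = 0.355 and 1.96 × √(0.442/16.5) = 0.321
- pooled variance: 1.96 × √(0.4758/13.5) = 0.368 and 1.96 × √(0.4758/16.5) = 0.333

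That is about 32-37 points, wider than the planned 26.

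**4. Type I error of an unadjusted final test.** With interim statistic z on n₁ patients and final total N, the conditional chance of rejecting under the null is

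CE(z, N) = 1 − Φ[(1.96√N − z√n₁)/√(N − n₁)] + Φ[(−1.96√N − z√n₁)/√(N − n₁)].

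The worst case takes, at each z, the permitted N that makes CE largest, and averages over the standard normal distribution of z (normal approximation).

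| Permitted final N | n₁ = 27 | n₁ = 33 |
|---|---|---|
| fixed at 110 | 5.00% | 5.00% |
| 110 to 165 | 5.42% | 5.50% |
| 110 to 220 | 5.64% | 5.76% |
| 55 to 110 | 6.18% | 6.42% |
| 55 to 220 | 6.82% | 7.18% |

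The lower limit of 55 reflects the patients already enrolled. The upper limits are assumptions, since the protocol sets none.

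**5. Uses of the look that do no damage.** Stopping only for harm leaves the chance of a false claim of benefit at or below 2.5%. A pre-specified rule that raises N only when conditional power is at least 50% (aiming at 80%, cap 165 or 220) gives 4.97-4.99% two-sided.

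**6. Order of the analysis plan and the look.** Enrolment began on May 23, 2016. At 56 or 44 a year, 55 patients are reached after 55/56 × 12 = 11.8 or 55/44 × 12 = 15 months, roughly mid-May to late August 2017. The article, published on September 7, 2017, still places the analysis plan in the future. Actual accrual is not reported and a manuscript predates its publication, so this shows only that a plan approved after the look is possible on the stated schedule.

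**The case against.** The strongest reply is that this is a safety review. The section is headed as one, and harm is the only stopping ground it describes. Boundaries, re-estimation rules and combination tests commonly sit in an analysis plan or board charter, neither of which is shown. All of that stands, so the absence of those details is not criticized here. What remains is the sentence itself, which expressly extends the unblinded look to sample size and design.

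Several stronger readings are tempting, and the document does not support them:

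- *The enrolment trigger inflates type I error.* It does not. It makes the interim estimate imprecise. For the same permitted range of N, the worst case is smaller with fewer evaluable patients (5.64% at 27 against 6.20% at 55, for N from 110 to 220).
- *The look is an efficacy test at 0.05.* Two such looks would give about 8.9-9.1% with 27-33 evaluable patients (8.3% with 55), but the protocol states no stop for benefit.
- *The analysis plan is due only before the final unblinding.* The text does not say which unblinding it means, nor that the plan's authors see the board's data.
- *The protocol claims half the information at the look.* It says only that half are enrolled. For harm, early data are useful: delirium scores on the composite and is known soon after surgery. The 27-33 concerns only the complete composite.

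**Conclusion.** The concern holds as a badly drawn clause, not as proven inflation. Open-ended advice on sample size or design, from unblinded comparative data that include components of the primary endpoint, is incompatible with a guaranteed 5% level for an unadjusted chi-square test. The possible excess is modest: at worst about 5.4-5.8% if N may only rise, up to double, and about 6.8-7.2% if N may move between 55 and 220. These figures take the most damaging N at every interim result and limits on N that the protocol does not state. Harm-only stopping adds nothing, and a suitable pre-specified rule need not.

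The second point is independent of the first. With about 27-33 complete composites, a half-width of 32-37 points cannot guide re-sizing for a 26-point effect. It rests on steady accrual and no wait for surgery; a wait would make it worse.

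**What to change.** - Reword Data safety analysis so that the unblinded look at 55 enrolled is for harm only, with no stop for efficacy. The final alpha then stays at 0.05.
- Base any sample-size review on the pooled, arm-blind event rate among patients with completed 6-month outcomes.
- If comparative re-sizing is wanted after all, pre-specify the rule together with a test that controls the error, such as a combination or conditional-error test, and tie the look to completed 6-month outcomes.
- State in Statistical analysis that the analysis plan is approved before the board's unblinded look.
- If the look has already been held, record what it covered and whether any change to size or design was advised.

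The cost is wording in the protocol, board charter and analysis plan, with no extra patients for the harm-only version. The downside is that the board gives up ad hoc unblinded re-sizing.
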